### Sample size

Presently, the cure rate for tuberculosis with the DOTS strategy is around 65% [2] in Cameroon, about 20% lower than the objective fixed by PNLT. Our hypothesis is that the cure rate in the SMS intervention group will reach 85%. For an attribution ratio of 1:1 in the two groups, 80% power, an alpha error of 5% and a two-sided test (effects may be interpreted independent of the way they go), we require a sample size of at least 166 participants [39], 83 in the SMS intervention group and 83 in the control group. Considering that the risk of loss to follow-up at the end of the study is important, we increased the sample size by 20%, giving 199 participants. Also, for the urban zone, we estimated that at least 90% of eligible people will have mobile phones and that at least 80% of them will consent to take part. The total number of eligible participants was therefore increased by 10% and another 20%, leading to a total of 260 participants.

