### Plan for data analysis

The results of this study will be reported following CONSORT standards [40] on randomized trials. A data entry mask developed using the Epi Data Entry program by the main investigator will be used to enter and control the quality of patient data. Analysis of the primary outcome will use the intention-to-treat approach, which includes all participants in their initial study group allocation. All participants for which there are no smear test results at 6 months will be considered not cured or cured (worst case or best case scenario). Results will be presented depending on the type of variable: means (± standard deviation) and medians (minimum and maximum) for continuous variables and percentages for categorical or binary variables.

The two groups will be described according to their baseline characteristics. Student’s test (*t*-test) will be used to calculate the difference between the two groups for continuous variables while the chi-square test will be used for categorical or binary variables. The association between study groups and cure rate will be analysed using a logistic regression model reporting the odds ratio and 95% CI.

Each individual characteristic, such as age, sex, level of education, socio-economic category, and HIV status, will be tested for an association with the cure status in a univariate analysis of the control group. Each characteristic that is significantly related with the outcome (*P* < 0.1) will be tested using a bivariate model that includes the study group, cure status and the potential confounder. If introducing the variable changes the odds ratio by more than 10%, then the variable will be considered as a potential confounder of the association and will be used in the final multivariate model.

The data from this study will be analysed using the SPSS programme (v21.0) or STATA (v11). Comparisons between the two groups will be expressed in terms of the odds ratio and the number needed to treat. Open questions in the questionnaire (especially problems observed during follow-up) will be analysed using the content analysis technique.

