## Trial status

The recruitment of patients began on 25 February 2013. We distributed 400 questionnaires in 16 tuberculosis treatment centres. Currently only 12 centres have begun recruiting patients. Of the 260 eligible patients required, 288 patients have now been included. To date, the recruitment of participants was stopped.

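### The steps from 166 to 260 are miscalculated and 260 is mislabelled; power for 65% versus 85% is not harmed, but the loss allowance does not match an analysis that keeps lost patients

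*Protocol article*

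**What the plan says.** The Sample size section of the protocol article states that "the cure rate for tuberculosis with the DOTS strategy is around 65"% and supposes that "the cure rate in the SMS intervention group will reach 85"%. With 1:1 allocation, "80% power, an alpha error of 5% and a two-sided test", it obtains 166 patients, 83 per arm. It then calls the risk of loss to follow-up important and says "we increased the sample size by 20%, giving 199 participants". No loss rate is given. Finally it assumes that at least 90% of eligible people have a mobile phone and at least 80% of those consent, and writes: "The total number of eligible participants was therefore increased by 10% and another 20%, leading to a total of 260 participants".

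Trial status reports progress against that last figure: "Of the 260 eligible patients required, 288 patients have now been included".

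On analysis, Plan for data analysis says "Analysis of the primary outcome will use the intention-to-treat approach, which includes all participants in their initial study group allocation". That section and Primary outcome both deal with patients who lack a final result by scoring them all as not cured or all as cured. Primary outcome calls these two extreme scenarios. Neither is named as the main one.

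The Background defines the cure rate as the share of cases that both complete six months of treatment and have a negative smear at six months.

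**The concern.** There are three separate problems.

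- **The inflation steps.** An allowance for a proportion lost, without a phone or not consenting is made by dividing by the proportion that remains. The section adds the percentage instead, which always gives too small a number.
- **The meaning of 260.** It is built as a count of eligible people before phone ownership and consent. Both are entry requirements under Participants and inclusion and exclusion criteria, so every included patient has already passed them. Comparing 288 included patients with 260 compares different populations, and the article never gives a clear number to randomise.
- **The purpose of the loss allowance.** Adding patients to replace those lost makes sense if the lost leave the analysis. Here they stay in, scored one way or the other. That changes the cure rates being compared, not the number analysed.

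At stake is how a result is read. A null worst-case result would be judged against an 80% power claim that was calculated for a different contrast.

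**Working it through.** **Inputs.** From Sample size: 65%, 85%, two-sided 5%, 80% power, 1:1, a 20% increase, 90% phone ownership, 80% consent. From Trial status: 288 included. Assumed here: 20% loss, equal in both arms, with 16.7% as the alternative.

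**1. The base figure reproduces.** With mean rate 0.75 and difference 0.20, the uncorrected size per arm is

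n = [1.96·√(2·0.75·0.25) + 0.842·√(0.65·0.35 + 0.85·0.15)]² / 0.20² = 72.4, so 73.

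With the continuity correction, n' = (n/4)·[1 + √(1 + 4/(n·0.20))]² = 82.1, so 83 per arm and 166 in total, as stated.

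**2. The loss step.** 166 × 1.2 = 199.2, the stated 199. With 20% loss, 199 × 0.8 = 159 remain, fewer than 166. Division gives 166/0.8 = 207.5, so 208. The figure 199 is right for a loss of 1 − 1/1.2 = 16.7%.

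**3. Phone ownership and consent.** 0.9 × 0.8 = 0.72.
- From 199: 199/0.72 = 276.4, so 277.
- From 208: 208/0.72 = 288.9, so 289.
- The stated 260 is approximate even by its own method: 199 × 1.1 × 1.2 = 262.7 and 199 × 1.3 = 258.7.

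The closeness of 289 (to approach) and 288 (included) is chance; they count different people.

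**4. Power for 65% versus 85% if lost patients are excluded.** Power = Φ{[d − c − 1.96·√(2p̄(1−p̄)/n)] / √[(p₁(1−p₁) + p₂(1−p₂))/n]}, where n is the number per arm and c = 1/n with the continuity correction, 0 without.

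| Included | Left after 20% loss | Corrected | Uncorrected |
|---|---|---|---|
| 260 | 208 | 89.3% | 92.1% |
| 288 | about 230 | 92.4% | 94.4% |

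**5. Power at 288 if lost patients are kept.** If 65% and 85% apply to patients followed and a fraction L is lost in each arm, the worst-case rates are (1 − L) × 0.65 and (1 − L) × 0.85. The best case adds L to each.

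| Scenario | Contrast | Corrected | Uncorrected |
|---|---|---|---|
| Worst case, L = 20% | 52% v 68% | 75.8% | 79.5% |
| Worst case, L = 16.7% | 54.2% v 70.8% | 80.3% | 83.5% |
| Best case, L = 20% | 72% v 88% | 90.5% | 92.8% |

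**6. The ceiling.** In the worst case the SMS arm cannot exceed 1 − L. At L = 15%, a rate of 85% needs every followed patient to be cured; above 15% it cannot be reached. At L = 20% the ceiling is 80%. If 65% already counts losses as not cured, the largest possible contrast is then 65% versus 80%, with power at 288 of 77.9% corrected and 81.7% uncorrected.

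**The case against.** The strongest reply is that the trial has ample patients. It included 288, well above the 208 that the corrected loss step requires, and recruitment has stopped. This stands. A reader might infer from the faulty steps that the stated 80% power is not delivered, and the documents do not support that. Using 260 as an enrolment figure recruits more patients than needed, so the mislabelling offsets the under-inflation. Power below 80% for 65% versus 85% needs either 199 randomised (159 evaluable, 78.6%) or 260 approached (260 × 0.72 × 0.8 = 150 evaluable, 75.7%). Neither happened, and both exceed 80% without the continuity correction (83.7% and 81.3%).

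It can also be said that 20% loss is nowhere stated. This stands too: 199 is wrong only if the 20% increase was meant to cover 20% loss, and at 16.7% loss the worst-case shortfall disappears. The phone and consent step has no such defence, because its percentages are stated.

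Third, the worst case is one of two bounds, and a trial need not have 80% power at its pessimistic extreme. That is fair as a matter of design. But the plan offers only these two treatments of missing final smears and does not say to which the 80% belongs.

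Finally, equal loss by arm is an assumption, and reminders might reduce loss in the SMS arm. The Background definition also suggests that 65% may already count non-completers as not cured, in which case 52% versus 68% would count the losses twice. Both points limit the worst-case figures and leave the mismatch in place.

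**Conclusion.** The point holds as an error of arithmetic and labelling, together with a mismatch between the loss allowance and the analysis. It is not a finding that the trial is underpowered.

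- On the stated percentages, the eligible pool should be 277 (from 199) or 289 (from 208), not 260. The number to randomise is 208 rather than 199 if 20% loss was intended.
- The 288 included patients are compared with a number that does not count included patients.
- Power for 65% versus 85% at 288 is 92–94% with 20% excluded.
- Power falls below 80% at 288 only in the worst-case analysis at about 20% loss, and only slightly: about 76–79.5% for 52% versus 68%, or 78–82% for 65% versus the 80% ceiling. At 16.7% loss the first of these contrasts has about 80–84%.

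The worst-case figures assume equal loss in both arms. The 52% versus 68% contrast also assumes that 65% and 85% refer to patients followed, which the article does not settle.

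**What to change.** Change the text as follows; no further patients are needed.

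1. State the assumed loss rate. For 20%, give 166 evaluable, 208 to randomise and 289 eligible people to approach.
2. In Trial status, report the 288 included against the number to randomise, not against 260.
3. Say whether 65% and 85% already count lost patients as not cured. If they do, the loss inflation is not needed for the worst-case analysis, and the 85% must be compatible with the loss expected in the SMS arm. If they do not, give the diluted worst-case contrast.
4. State power at 288 for both the worst-case and best-case analyses, with the assumptions behind each and whether the continuity correction is used.

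The cost is that the stated worst-case power may be slightly below 80%.

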### Randomisation

In the first step, participants will be stratified according to recruitment centre. The different treatment centres will be alphabetically coded (A, B, C and so on) and participants attached to each centre will be given numerical codes (for example, patients in centre A will be numbered A001, A002 and so on).

Randomisation will be carried out using a computer program by the main investigator. Participants who are eligible and who have consented to participate in the study will be registered. Their study identifier and telephone number will be communicated to the main investigator and to the secretary, for their randomly allocation by centre into one of the two groups (intervention or control) and for the continuous updating of the mailing of SMS respectively.

The health staff in the hospitals will not be involved in the allocation of participants into groups. This prevents allocation bias and minimises the risk of selection bias (simple blind).

### Feasibility of the study

The number of new cases of TPM + in Cameroon was 14,464 in 2010, that is an average of 3,616 new cases per trimester. The Littoral (22%) and Centre (20%) regions have half of the new cases, mainly in Douala 17% (the economic capital) and Yaoundé 13% (the political capital). By recruiting participants only in Yaoundé, we will reach 13% of the 3,616 new cases of TPM + in a trimester, that is 471. A recruitment phase of 4 months should therefore be long enough to recruit a sufficient number of participants to the study.

### Data collection

Health staff taking care of participants in the study will collect data using patient follow-up files developed by the research team. These will contain all the necessary questionnaires, scales and lists of problems. The follow-up files will be kept with the participants’ health records. A marker will be placed on the file of each participant to reduce the risk of them being ‘forgotten’ by health staff during the study. Forms in the file will be completed in French for each visit (the day of inclusion and the second, fifth and sixth months).

Before the onset of recruitment, a meeting will be held with the staff members of the treatment centres. This will inform them of and validate the strategies for the implementation of the study (inclusion of participants, collection of data, use of VAS by patients to evaluate adherence, transmission of data and so on).

During the recruitment phase, a secretary will be responsible for collecting telephone numbers from the participant study files twice a week from each Treatment and Diagnostic Centre. These will be entered into the SMS database. The secretary will also collect socio-demographic data (from the day of inclusion), smear test results (from the day of inclusion, and the second, fifth and sixth months), punctuality data and results of resistance to rifampicin tests (Genexpert).

At least two sessions to supervise staff members (2 months and 6 months after the onset of recruitment) will be carried out in each centre so that data collection remains effective and consistent. Treatment centres facing problems will receive additional training and supervision at appropriate intervals. After recruitment, the secretary will collect data once a week to keep statistics and participant registers up to date. At the final follow-up (during the third visit at the end of the sixth month), health staff will administer a self-evaluation questionnaire on the degree of satisfaction to the participants.

### Plan for data analysis

The results of this study will be reported following CONSORT standards [40] on randomized trials. A data entry mask developed using the Epi Data Entry program by the main investigator will be used to enter and control the quality of patient data. Analysis of the primary outcome will use the intention-to-treat approach, which includes all participants in their initial study group allocation. All participants for which there are no smear test results at 6 months will be considered not cured or cured (worst case or best case scenario). Results will be presented depending on the type of variable: means (± standard deviation) and medians (minimum and maximum) for continuous variables and percentages for categorical or binary variables.

The two groups will be described according to their baseline characteristics. Student’s test (*t*-test) will be used to calculate the difference between the two groups for continuous variables while the chi-square test will be used for categorical or binary variables. The association between study groups and cure rate will be analysed using a logistic regression model reporting the odds ratio and 95% CI.

Each individual characteristic, such as age, sex, level of education, socio-economic category, and HIV status, will be tested for an association with the cure status in a univariate analysis of the control group. Each characteristic that is significantly related with the outcome (*P* < 0.1) will be tested using a bivariate model that includes the study group, cure status and the potential confounder. If introducing the variable changes the odds ratio by more than 10%, then the variable will be considered as a potential confounder of the association and will be used in the final multivariate model.

The data from this study will be analysed using the SPSS programme (v21.0) or STATA (v11). Comparisons between the two groups will be expressed in terms of the odds ratio and the number needed to treat. Open questions in the questionnaire (especially problems observed during follow-up) will be analysed using the content analysis technique.

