### Cure status

A participant is considered to be:

•Cured, if they have a negative smear test after 6 months of treatment.

•Not cured or a treatment failure if they have a positive smear test after 5 months of treatment.

•Transferred, if they are referred to continue treatment in another Treatment and Diagnostic Centre out of the study zone.

•Dead, if they die between the screening phase and the end of treatment, regardless of the cause of death.

•Lost to follow-up, if they receive at least one month of treatment and are not in any of the classes above.

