**Secondary**			
**Adherence of patients to treatment (second, fifth, sixth months)**			
Drug prescriptions collected and doses taken (visual analogue scale)	Percentage of adherence to treatment during the last 30 days	Continuous	*t*-test
Keeping appointments		Binary	Chi-square
Punctuality of appointments		Categorical	Chi-square
**Multi-drug-resistant tuberculosis (fifth and sixth months)**	Percentage of patients with multi-drug-resistant tuberculosis	Binary	Chi-square
**Satisfaction (sixth month)**	Satisfaction	Continuous	*t*-test

The status of each patient will be based on the results of smear tests carried out in the second, fifth and sixth months in the treatment centre. At the fifth month, two scenarios are possible. If the smear test is negative, treatment continues during the sixth month. At 6 months, the final smear test is done to see if the patient is cured. If this test is negative, the patient is classified as cured.

If the test at 5 months is positive, a second smear test will be performed to confirm the result (which is not mandatory for this study). At this moment, the patient will be considered as a treatment failure and classified as not cured in the study.

Participants lost to follow-up or referred to other treatment centres, will be considered cured (best case) or not cured (worse case) as two extreme statistical scenarios.

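### The missing-smear rule in the analysis plan is wider than the outcome definitions, so its best case counts deaths before month 6 and month-5 failures without a 6-month smear as cured

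*Protocol article*

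**What the plan says.** Three places in the protocol article bear on who counts as cured.

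- **Plan for data analysis.** The primary outcome is analysed by intention to treat in all allocated participants. "All participants for which there are no smear test results at 6 months will be considered not cured or cured", with worst case and best case named as the two scenarios. The only condition is that the 6-month smear is absent.
- **Primary outcome (text below Table 1).** The two scenarios have a narrower scope: "Participants lost to follow-up or referred to other treatment centres, will be considered cured (best case) or not cured (worse case"). For a positive month-5 smear the text is definite: "At this moment, the patient will be considered as a treatment failure and classified as not cured in the study". The final smear is described only on the branch where the month-5 smear was negative.
- **Cure status.** Cured requires a negative smear after 6 months of treatment. A month-5 positive is classed as follows: "Not cured or a treatment failure if they have a positive smear test after 5 months of treatment". Death is a separate class: "Dead, if they die between the screening phase and the end of treatment, regardless of the cause of death". Loss is what remains: "Lost to follow-up, if they receive at least one month of treatment and are not in any of the classes above".

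The Background section also defines the cure rate by completion of 6 months of treatment together with a negative 6-month sputum test.

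**The concern.** Best-case and worst-case bounds are meant for outcomes that are unknown. A death before month 6 and a positive smear at month 5 are known outcomes, and neither is a cure under the article's own definitions. The analysis plan selects participants by the absence of a 6-month smear, not by the absence of knowledge about the outcome, so it takes these participants in with the lost and the transferred.

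The primary outcome is at stake. The article describes the two scenarios without ranking them, so the best case may carry as much weight as the worst case when the result is read. The Background section links irregular adherence to treatment failure and to mortality. The participants who would be recoded are thus among those in whom a reminder would be expected to make a difference.

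**Working it through.** **Reproducing the plan's own figure.** Inputs from Sample size: 65% and 85% cure, two-sided 5%, 80% power, 1:1.

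Uncorrected size per arm, with mean proportion 0.75:

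n = [1.96·√(2·0.75·0.25) + 0.8416·√(0.65·0.35 + 0.85·0.15)]² / 0.20² = (1.2003 + 0.5015)² / 0.04 ≈ 72.4, so 73.

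With continuity correction: (n/4)·[1 + √(1 + 4/(n·0.20))]² = (72.4/4)·(1 + 1.130)² ≈ 82.1, so 83 per arm and 166 in total. This matches the article. The planned 20-point difference is a sound starting point for the illustration below.

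**Setting the rules side by side.**

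| Participant | Cure status and Primary outcome | Analysis plan, worst case | Analysis plan, best case |
|---|---|---|---|
| Died before month 6 | Dead; cannot meet cured; not among those given the two scenarios | Not cured | Cured |
| Month-5 positive, no 6-month smear | Not cured | Not cured | Cured |
| Month-5 positive, 6-month smear negative | Not cured (Primary outcome) | Rule does not apply | Rule does not apply |
| Transferred, or lost after at least one month; no 6-month smear | Both scenarios | Not cured | Cured |
| Lost before one month | No class; not clearly reached | Not cured | Cured |

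The conflict is in the best-case column of the first two rows. It is explicit for month-5 failures. For deaths it follows from the definitions, since no sentence says in words that a death is not cured.

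**Size, under stated assumptions.** The article gives no expected number of deaths or month-5 failures. Let q be the share of true non-cures in each arm who died or failed at month 5 and have no 6-month smear. Take q as equal in both arms and assume no other missing data. The best-case cure rate is p + q·(1 − p), so the difference is (1 − q)·20 points.

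Power uses the normal approximation without continuity correction: Φ{[d·√n − 1.96·√(2·p̄·(1 − p̄))] / √[p₁(1 − p₁) + p₂(1 − p₂)]}. It is shown at the planned 83 per arm and at 144 per arm (288/2, from Trial status).

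| q | Control | SMS | Difference (points) | Power, 83 per arm | Power, 144 per arm |
|---|---|---|---|---|---|
| 0 | 65% | 85% | 20 | 85% | 98% |
| 0.25 | 73.75% | 88.75% | 15 | 70% | 91% |
| 0.50 | 82.5% | 92.5% | 10 | 49.5% | 73% |
| 0.75 | 91.25% | 96.25% | 5 | 26% | 42% |

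The row q = 0 is the result when these participants stay not cured. If the shares differ between arms, the difference is 0.35·(1 − q in control) − 0.15·(1 − q in SMS), which can be smaller or larger than the values shown.

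**The case against.** The strongest reply is that the sentence in the analysis plan is condensed journal wording for missing outcomes, and that the more specific text under Primary outcome governs. On that reading a month-5 failure is settled at month 5 and never reaches the missing-data rule. This is a reasonable guess at the intention. But nothing in the article says that one section yields to the other, and the unrestricted wording stands in the section from which the analysis would be programmed. For deaths the reply is weaker, because the Primary outcome section does not mention them. Aligning the two sections would still leave their handling unstated.

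Several parts of the other side stand in full:

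- Only the best case is affected, and the article itself calls the scenarios extreme. The worst case keeps deaths and failures as not cured.
- The number of month-5 failures affected is unknown. The section on implementation schedules smears at months 2, 5 and 6 for participants generally, and nothing says that failures never have a 6-month smear.
- A reader might infer from Cure status that a month-5 positive with a negative 6-month smear is both cured and not cured. The Primary outcome section resolves this: it fixes the month-5 positive as not cured and reaches cured only after a negative month-5 smear.
- A reader might infer that participants lost before one month drop out of the analysis. They lack a class label, but the broad rule in the analysis plan covers them.

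**Conclusion.** The rule is wrong as written and should be fixed before outcomes are analysed. Followed literally, the best-case analysis of the primary outcome counts deaths before month 6 and month-5 failures without a 6-month smear as cures. This contradicts the outcome definitions.

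The reduction of the difference to 15, 10 or 5 points holds for assumed shares of 25%, 50% and 75%, equal in both arms and with no other missing data. The article supplies none of these shares.

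A reader might go further and infer that best-case cure approaches 100% in both arms, or that the trial loses all information on failure and death. The documents do not support either. The first needs very few positive 6-month smears, a count that the article does not give; over the range above, control cure is 73.75% to 91.25%. The second overlooks the worst case, which keeps that information. Part of any narrowing in the best case would also come from lost and transferred participants, and there it is legitimate.

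**What to change.** In the Plan for data analysis:

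1. Limit the best-case and worst-case scenarios to participants whose outcome is unknown, namely those transferred or lost without a known result. Name those lost before one month of treatment explicitly. The lost class in Cure status omits them, so a restriction by class label alone would leave them out.
2. State that deaths and month-5 positives count as not cured in both scenarios for the primary analysis. For deaths this has to be written out, since the Primary outcome section is silent on them.

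In Cure status, word the cured and not-cured classes to agree with the Primary outcome section, which already gives a month-5 positive precedence.

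The cost is a few lines of text. The planned records already hold the smear results, and no sample size or trial procedure changes. Recruitment has stopped with 288 included, so the wording should be settled and dated before outcomes are analysed; otherwise the choice between the two rules would be made with results in view.

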### Outcomes and plan for analysis

#### Primary outcome

The primary objective (Table 1) is to measure the difference in cure rate at 6 months between the SMS intervention group and control group.

**Table 1 T1:** Outcomes of the study

**Outcomes**	**Measure of outcomes**	**Type**	**Statistical analysis**

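### Allocation is stratified by centre, but the stated analyses of cure leave centre out, and the difference in cure rate has no planned estimate with a confidence interval

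*Protocol article*

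**What the plan says.** **Allocation.** The Randomisation section states: "In the first step, participants will be stratified according to recruitment centre". Study design also describes 1:1 randomisation by centre. Neither section mentions blocks or another balancing method. Sixteen centres were planned; Trial status reports 12 recruiting and 288 patients included.

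**Analysis of cure.** Table 1 lists chi-square and logistic regression for cure at the sixth month. Plan for data analysis repeats the chi-square test for binary variables and adds: "The association between study groups and cure rate will be analysed using a logistic regression model reporting the odds ratio and 95% CI". Covariates are individual characteristics; age, sex, education, socio-economic category and HIV status are given as examples. A characteristic enters the final model only if it is associated with cure in the control group (P < 0.1) and then changes the odds ratio by more than 10%. Centre is not mentioned.

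**Effect measure.** The primary objective, as worded under Primary outcome, "is to measure the difference in cure rate at 6 months between the SMS intervention group and control group". Plan for data analysis says that binary variables will be presented as percentages and that group comparisons will be expressed as the odds ratio and the NNT. No confidence interval is mentioned for a difference in cure rate.

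**The concern.** When allocation is balanced within strata and the strata differ in outcome, the balance removes between-stratum variation from the treatment contrast. An unstratified test still counts that variation in its standard error. The test is then conservative and can miss a real benefit somewhat more often than it should.

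The covariate screen does not repair this. Centre is not an individual characteristic, and a stratification factor should be fixed in advance rather than admitted by a data-driven confounder rule.

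Separately, the quantity that the primary objective names would have no interval of its own. At the planned rates the odds ratio is about three while the cure rate rises by less than a third, so an odds ratio is easily misread as a ratio of cure rates.

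**Working it through.** **1. The plan's own sample size.** Inputs from the Sample size section: 65% and 85% cure, "For an attribution ratio of 1:1 in the two groups", and "80% power, an alpha error of 5% and a two-sided test".

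- Without continuity correction: n = [1.96 × √(2 × 0.75 × 0.25) + 0.8416 × √(0.65 × 0.35 + 0.85 × 0.15)]² / 0.20² = (1.2003 + 0.5014)² / 0.04 = 72.4, so 73 per arm.
- With continuity correction: (72.4 / 4) × [1 + √(1 + 4 / (72.4 × 0.20))]² = 82.1, so 83 per arm and 166 in total.

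This reproduces the stated figure ("we require a sample size of at least 166 participants"). The present point does not change it.

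**2. Effect measures at the planned rates.**

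- Risk difference: 0.85 − 0.65 = 0.20; NNT: 1 / 0.20 = 5
- Risk ratio: 0.85 / 0.65 = 1.31
- Odds ratio: (0.85 / 0.15) / (0.65 / 0.35) = 3.05

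**3. Effect of leaving centre out.** The article gives neither the centre-to-centre variation nor the block method, so both are assumed. The simulation used 8,000 trials per scenario, unequal centre sizes, and a normal centre effect on the log-odds of cure. The mean control cure rate was 65%. An SD of 0.5 puts 90% of centres between about 46% and 81% cure; an SD of 1.0 puts them between about 29% and 92%.

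No treatment effect, 260 patients, 16 centres, blocks of 4 within centre:

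| Centre SD | Unadjusted SE | Actual SD of the difference | Ratio | Chi-square type I error | CMH type I error |
|---|---|---|---|---|---|
| 0.5 | 0.0588 | 0.0570 | 1.03 | 4.6% | 5.0% |
| 0.8 | 0.0586 | 0.0551 | 1.06 | 3.6% | 4.6% |
| 1.0 | 0.0584 | 0.0542 | 1.08 | 3.5% | 5.0% |

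At SD 0 to 0.3 the unadjusted SE is about right. The Monte Carlo error of a 5% rejection rate is √(0.05 × 0.95 / 8000) = 0.24 points. The Mantel-Haenszel difference has almost the same actual SD as the crude difference (0.0541 versus 0.0542 at SD 1.0). Under blocking, therefore, the crude estimate itself is not less precise; its stated uncertainty is too large.

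Power with blocks of 4, chi-square to CMH:

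| Scenario | SD 0.5 | SD 0.8 | SD 1.0 |
|---|---|---|---|
| 65% v 85%, N = 260, 16 centres | 97.0 to 97.1% | 97.1 to 97.6% | 96.9 to 97.8% |
| 65% v 85%, N = 166, 16 centres | 85.9 to 86.1% | 87.3 to 88.6% | 87.2 to 89.3% |
| 65% v 80%, N = 288, 12 centres | 82.7 to 83.5% | 82.5 to 84.9% | 82.3 to 86.4% |

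The last row (6,000 trials per scenario) uses a smaller effect than the protocol's hypothesis, to show a case where power is not already near its ceiling.

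**4. The same check without blocks.** With simple randomisation within centre (N = 260, 16 centres), the chi-square type I error is 4.7% to 5.4% over the whole SD range. With no centre effect, CMH then loses power at 65% versus 85%: 96.3 to 95.2% at N = 260 and 85.8 to 82.4% at N = 166.

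**The case against.** **The harm is conditional.** The unadjusted standard error is too large only if allocation is balanced within centre and centres truly differ in cure. The article states stratification and a 1:1 ratio but no balancing method. Centre differences are inferred: drug supply in the first two months is weekly or monthly, but the article does not say that this varies by centre, and all centres are in one city under one national programme. This stands.

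**The direction is safe and the gain is small.** Where the mismatch bites, it does not create false positives. At the protocol's own 65% versus 85%, stratifying gains at most about 1 point at 260 patients, and it can cost power with many small centres that do not differ. This stands too.

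**The absolute effect is already visible.** Percentages and the NNT are planned, and the NNT is the reciprocal of the risk difference. A reader might infer that the plan reports only an odds ratio; it does not. What remains is narrower: the difference itself with a confidence interval, which an interval for the NNT would also need.

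**A condensed article leaves model detail to the full plan.** An analysis plan that is not shown may include centre, and the covariate list is open-ended. But the article does state its tests and its rule for adding covariates, and neither uses the factor by which it randomises. That stated choice is the point here.

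**Conclusion.** The point holds as a modest mismatch between design and analysis. Centre governs the allocation and is absent from the stated analyses of cure, and the effect named as the primary objective has no planned interval.

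Its size depends on two assumptions that the article does not settle. With balance within centre and a between-centre logit SD of 0.5 to 1.0, the unadjusted standard error under no effect is about 3% to 8% too large at 260 patients, and the chi-square type I error is about 4.6% down to 3.5%. The power gain from stratifying is up to about 1 point at 65% versus 85% with 260 patients, and about 1 to 4 points at 65% versus 80% with 288. Without centre differences, or with unblocked allocation, the chi-square test keeps its size.

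A reader might infer that the planned standard error is simply wrong, or that the primary result would be invalid. The documents do not support that: they show neither within-centre balance nor centre variation in cure, and any error is conservative.

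**What to change.** - Make the primary test of cure a Cochran-Mantel-Haenszel test stratified by centre.
- Report the Mantel-Haenszel risk difference with its 95% CI as the primary effect, and derive the already planned NNT from it.
- Include centre in the logistic model by one method chosen in advance, for example conditional logistic regression. State that the odds ratio is then conditional on centre and need not equal the crude one.
- Fix a rule for pooling very small centres before unblinding.
- State the balancing method used within centre, since the size of the issue depends on it.

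The cost is wording only: every participant code already carries the centre letter, and no new data are needed. The downside is a power loss of about 1 to 3 points if centres do not differ and allocation within centre was unblocked. The pooling rule should limit this, because the loss comes from small centres with unequal arms.
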